### Kidney retrieval

All kidneys will be retrieved by the UK national retrieval teams. Following in situ flushing of the abdominal organs with hyperosmolar citrate (HOC) solution or University of Wisconsin (UW) solution, kidneys will be removed and then placed individually in preservation solution and packed in ice. The perfusion solution used will be recorded.

### vivo normothermic perfusion

The EVNP circuit has been designed using paediatric cardiopulmonary bypass technology (Medtronic, Watford, UK) and consists of a centrifugal blood pump (Bio-pump 560), a heat exchanger, a venous reservoir (Medtronic), 1/4 inch Polyvinyl chloride (PVC) tubing and an Affinity membrane oxygenator (Medtronic). The hardware includes a speed controller, a TX50P flow transducer and a temperature probe (Cole-Parmer, London, UK). Two infusion pumps are also incorporated into the system.

### Perfusate

The circuit will be primed with perfusate solution (Ringer's solution, Baxter Healthcare, Thetford, Norfolk, UK) and one unit of O-positive or O-negative packed red cells from the blood bank. Mannitol 10% (Baxter Healthcare), dexamethasone 8 mg (Organon Laboratories, Cambridge, UK) and heparin (CP Pharmaceuticals, Wrexham, UK) will be added to the perfusate. Sodium bicarbonate 8.4% (Fresenius Kabi, Cheshire, UK) will be added to normalise the pH. A nutrient solution (Synthamin 17, Baxter Healthcare) with sodium bicarbonate 8.4%, insulin (Novo Nordisk, Denmark) and multivitamins (Cernevit, Baxter Healthcare) will be infused into the circuit at a rate of 20 mL/hour. Prostacyclin 0.5 mg (Flolan, Glaxo-Wellcome, Middlesex, UK) will be infused into the arterial arm of the circuit at a rate of 5 mL/hour and glucose 5% (Baxter Healthcare) at 5 mL/hour. Ringer's solution will be used to replace urine output mL for mL.

### Perfusion chamber

Kidneys undergoing EVNP will be placed in a custom-designed sterile perfusion chamber and the renal artery and vein will be cannulated and primed with cold 0.9% sodium chloride.

### Perfusion parameters

Kidneys will be perfused at a set mean arterial pressure (75 mm Hg). The plasma-free red cell-based perfusate will be circulated from the venous reservoir through the centrifugal pump into the membrane oxygenator, where it is oxygenated and also warmed to 35–36^°^C. It will then flow through the arterial limb of the circuit to the renal artery. Venous return from the renal vein will be fed back into the reservoir.

Renal blood flow (RBF) will be monitored continuously during EVNP. Intrarenal resistance will be calculated (mean arterial pressure/RBF) every 5 min until the end of perfusion. The total urine output will be recorded. Blood gas analysis will be used to measure the acid–base balance pre-EVNP and post-EVNP.

### Postperfusion

After EVNP, kidneys will be flushed with ∼500 mL of cold (4^°^C) HOC (Baxter Healthcare, UK) to remove the perfusate and then placed back in ice until transplanted. Prior to transplantation, the arterial Carrel patch may have to be excised along with a short segment of vein in order to remove the cannula ligature sites.

### EVNP assessment scoring

An assessment score will be recorded for all kidneys undergoing EVNP but will not be used to make decisions about the suitability of kidneys for transplantation (table 1).^13^

**Table 1 BMJOPEN2016012237TB1:** Ex vivo normothermic perfusion (EVNP) score

EVNP score	
Macroscopic appearance	Points
Excellent perfusion with global and even pink appearance	1 point
Moderate perfusion with some areas of patchy or mottled perfusion	2 points
Poor perfusion with a globally mottled and purple appearance	3 points
Mean renal blood flow (mL/min/100 g) <50 mL/min/100 g	1 point
Mean renal blood flow (mL/min/100 g) >50 mL/min/100 g	0 point
Total urine output (mL) <43mL/hour	1 point
Total urine output (mL) >43mL/hour	0 point

Scores for macroscopic appearance, renal blood flow and urine output will be added to yield an overall assessment score ranging from 1 (the highest quality) to 5 (the lowest quality).

### Transplantation

This will be performed using standard techniques. Anaesthesia will be given according to local protocols. Kidneys will be transplanted into either iliac fossa with anastomosis of the artery to the common, external or internal iliac arteries. The vein will be anastomosed to either the common or the external iliac vein. The ureteric anastomosis will be performed as an extravesical onlay over a double J stent.

### Immunosuppressive therapy

All centres will use similar immunosuppressive protocols as follows: patients will receive 20 mg of basiliximab intravenously pretransplant and 20 mg intravenously on postoperative day 4. Patients will receive a bolus of methylprednisolone intravenously at induction of anaesthesia using a dosage according to local practice. The post-transplant oral prednisolone regimen will also be according to local practice.

Patients may be treated with either tacrolimus or cyclosporine according to local protocols. There will be no restriction on the formulation of the prescribed calcineurin inhibitors. Tacrolimus will be prescribed to achieve target trough levels of 3–12 ng/mL. Cyclosporine will be prescribed to achieve target trough levels of 100–250 ng/mL. The first dose of calcineurin inhibitor may be given preoperatively or postoperatively. All patients will receive mycophenolate as either mycophenolate mofetil (Cellcept) at a starting dose of at least 1 g/day or mycophenolate sodium (Myfortic) starting at a dose of at least 720 mg/day.

Antimicrobial and antithrombotic prophylaxis will be given according to local protocols. It is expected that patients will also receive prophylaxis against *Pneumocystis jirovecii* pneumonia, oral candidiasis and cytomegalovirus (valganciclovir for 100 days in CMV-positive donor to CMV-negative recipient transplants).

### Outcomes

#### Primary outcome measure

The primary outcome measure is DGF defined as the need for dialysis in the first 7 days post-transplantation.^18^

#### Secondary outcome measures

The secondary outcome measures include incidences of primary non-function (PNF) defined as the permanent lack of allograft function from the time of transplantation (This will include graft losses due to irreversible rejection and vascular thrombosis. The cause of graft loss will be recorded.); the duration of DGF in days; functional DGF (fDGF) defined as <10% fall in serum creatinine for 3 consecutive days in the first week post-transplant; creatinine reduction ratio day 2 (CRR2=creatinine day 1−creatinine day 2/creatinine day 1) and CRR5 (CRR5=pretransplant creatinine−creatinine day 5/pretransplant creatinine);^19^ length of hospital stay, rates of biopsy-proven acute rejection rate and measures of renal function (serum creatinine and estimated glomerular filtration rate (eGFR)) at 1, 3, 6 and 12 months post-transplant. Patient survival (time from transplant to death) and allograft survival (time from transplant to graft loss or return to dialysis) will be recorded. The EVNP score will be calculated for each kidney undergoing EVNP (table 1). The predictive value of this assessment score on graft function and outcome will be evaluated. A clinical decision on the suitability of the kidney for transplantation will be made using normal criteria prior to perfusion. However, the EVNP assessment score will be taken into consideration. Arterial and venous samples will be collected during perfusion and used to measure oxygen consumption, acid–base balance and concentrations of sodium, potassium, glucose, lactate and calcium. Concentrations of sodium and potassium will also be measured in the urine at the end of EVNP.

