This study will investigate the effect of 60 min EVNP in kidneys from DCD donors compared with the traditional technique of static cold storage.

The primary outcome measure will be DGF defined as the need for dialysis in the first 7 days post-transplantation. Secondary outcome measures will include more sensitive measures of renal function over the first 7 days post-transplant, length of hospital stay, graft and patient survival at 1 year and rates of acute rejection. Fibrosis, inflammatory markers and urinary biomarkers will also be examined in tissue, blood and urine.

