#### Secondary outcomes

*PNF*: The number of patients experiencing PNF in each arm will be compared using Fisher's exact text. The cause of graft loss will be tabulated by arm. The duration of DGF in days will be summarised using the Kaplan-Meier estimate of the duration of DGF for all those who experienced DGF and compared using a log-rank test.

*Outcome measures*: The number of patients that experience functional DGF will be compared using Fisher's exact test. The CRR2 and CRR5 will be compared by arm using a two-sample t-test. The length of hospital stay, defined from admission to discharge, will be estimated using the Kaplan-Meier method, with deaths in hospital censored, and compared between arms using the log-rank test.

*Biopsy-proven acute rejection rate*: The number of patients in each arm will be compared using Fisher's exact test. Longitudinal changes in serum creatinine and eGFR will be separately assessed at 1, 3, 6 and 12 months post-transplant and mean values compared using two-way analysis of variance with repeated measures for patients in each arm of the trial. Any difference between arms in the way serum creatinine and eGFR change over time will also be assessed using this model. Patient survival (time from transplant to death) and allograft survival (time from transplant to graft loss or return to dialysis) will be analysed using a Kaplan-Meier estimate of the probability of an event after 12 months and a log-rank test. Time to graft loss or return to dialysis will be modelled.

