### Analysis population and missing data

Normally if a patient experiences DGF, they would remain in hospital for a minimum of 7 days. Hence, for pragmatic reasons, if a patient is discharged from the hospital prior to 7 days post-transplant and the patient is known to be alive at 7 days post-transplant, then such patients will be imputed to have not experienced DGF. Some patients may also withdraw consent, be withdrawn or die during the conduct of the trial. In any of these cases, it is impossible to know whether such patients are either less or more likely to experience DGF had they not experienced early censoring. Sensitivity analyses will be performed to account for this.

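### Functional DGF, CRR2 and CRR5 have no rule for patients dialysed in the measurement window, so dialysis-driven creatinine falls can count as graft function

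*Protocol article*

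**What the plan says.** The protocol article's Introduction presents the early secondary outcomes as "more sensitive measures of renal function over the first 7 days post-transplant". The Secondary outcome measures section then writes three of them out in full: "functional DGF (fDGF) defined as <10% fall in serum creatinine for 3 consecutive days in the first week post-transplant", "CRR2=creatinine day 1−creatinine day 2/creatinine day 1" and "CRR5=pretransplant creatinine−creatinine day 5/pretransplant creatinine". The ratios are printed without brackets. I read each as the difference divided by the earlier value.

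The Secondary outcomes part of the analysis section sets the tests: "The number of patients that experience functional DGF will be compared using Fisher's exact test", and "The CRR2 and CRR5 will be compared by arm using a two-sample t-test".

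None of this says what happens when a patient is dialysed between the creatinine samples. The nearest rule, under Analysis population and missing data, concerns the primary outcome: patients discharged before day 7 and known to be alive at day 7, "then such patients will be imputed to have not experienced DGF".

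The primary outcome covers the same week: "The primary outcome measure is DGF defined as the need for dialysis in the first 7 days post-transplantation". The sample size section plans for this in 50% of cold storage patients and 35% of EVNP patients.

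**The concern.** Dialysis removes creatinine regardless of graft function. A formula that reads any fall in creatinine as recovery therefore credits the machine's work to the graft. This will be common here, since up to half of one arm is expected to be dialysed. It will also be unequal between arms if EVNP does what the trial hopes.

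Two consequences follow. A graft poor enough to need repeated dialysis may never show three successive days without a 10% fall. It is then DGF-positive but fDGF-negative, which undermines a measure meant to be more sensitive than DGF. And a patient dialysed before the day 5 sample gets a higher CRR5 than the graft has earned. Both flatter the arm with more dialysis, so a real EVNP effect on these two outcomes would be understated.

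**Working it through.** **Inputs from the document.** The three definitions, the two tests, and the planned dialysis rates of 50% and 35%. No figure is stated for fDGF or CRR, so there is none to reproduce. The planned rates agree with the stated effect: (50 − 35)/50 = 30% relative reduction. The sample size is not at issue. At two-sided 5% and 80% power, the usual two-proportion formula gives 340 in total, or 366 with continuity correction. An O'Brien–Fleming inflation of about 1.017 for three looks takes 366 to about 372, near the stated 376, and 376/0.94 = 400.

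**Step 1: direction in one patient.** Assume a graft with no function, creatinine 600 before transplant (units cancel) and rising 100 a day, with each session removing 50%. I read fDGF as three successive daily changes that each show less than a 10% fall.

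- No dialysis: day 5 = 1100, so CRR5 = (600 − 1100)/600 = −0.83. fDGF: yes.
- Sessions on days 2 and 5: the values for days 1 to 5 are 700, 400, 500, 600, 350, so CRR5 = (600 − 350)/600 = 0.42. No three successive days lack a 10% fall, so fDGF: no.

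| Sessions on days | fDGF | CRR2 | CRR5 |
|---|---|---|---|
| none | yes | −0.14 | −0.83 |
| 1 | yes | −0.29 | −0.25 |
| 2 | yes | 0.43 | −0.17 |
| 2, 5 | no | 0.43 | 0.42 |
| 3, 6 | no | −0.14 | −0.08 |
| 1, 3, 5 | no | −0.29 | 0.60 |
| 2, 4, 6 | no | 0.43 | 0.33 |

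The fDGF classification was the same for removal of 30%, 40%, 50% and 60%. CRR5 exceeded −0.83 under every dialysis schedule tried. A single session, or two on days 1 and 2, left the patient classed as fDGF; spaced repeated sessions did not. CRR2 moved both ways: a session before the day 1 sample gives (350 − 450)/350 = −0.29, and one between the two samples gives (700 − 400)/700 = 0.43.

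**Step 2: effect on the fDGF comparison.** Assume every dialysed patient would be fDGF if dialysis did not mask it, a masked share m that is equal in both arms, and a share q of undialysed patients with fDGF. Then cold storage minus EVNP = [0.50(1 − m) + 0.50q] − [0.35(1 − m) + 0.65q] = 0.15(1 − m − q).

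- q = 10%: 13.5 points at m = 0, 6.0 at 50%, 0 at 90%, −1.5 at 100%. With 188 per arm and a normal approximation, power is about 75% at m = 0 and 26% at m = 50%.
- q = 20%: 12.0 points at m = 0, 4.5 at 50%, −3.0 at 100%.

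**Step 3: effect on mean CRR5.** A fractional fall d in day 5 creatinine raises CRR5 by d × (day 5 / pretransplant creatinine). If a share p of dialysed patients, equal in both arms, had dialysis before the day 5 sample, the bias towards cold storage is 0.15 × p × d × that ratio.

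- With p = 1 and ratio 1, d = 10%, 20%, 30% and 40% give 1.5, 3.0, 4.5 and 6.0 percentage points.
- With p = 1 and the ratio 1100/600 = 1.83 from Step 1, d = 10% gives 0.15 × 0.10 × 1.83 = 2.75 points and d = 40% gives 11.0.
- A p below 1 shrinks all of these in proportion.

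For scale, assume true mean CRR5 of 0.45 in undialysed and −0.05 in dialysed patients. The true arm difference is 0.15 × 0.50 = 0.075. It falls to 0.030 if dialysis adds 0.3 to CRR5, to 0 if it adds 0.5, and to −0.015 if it adds 0.6.

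**The case against.** The article says that a full statistical analysis plan will give the detail, and handling of dialysed patients is often placed there. The CRR definitions also cite a source that may carry its own convention. This stands in part: an unseen plan could add a rule. But the article does not leave these outcomes open. It states complete formulas, and a plan that applied them faithfully would reproduce the problem.

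A reader might go further and infer any of the following, none of which the document supports:

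- That all dialysed patients look like recovering grafts. In the model a single session left fDGF status unchanged, and the document gives no number of sessions per patient. The 50% and 35% are ceilings on who could be misclassified.
- That CRR2 is biased against EVNP. Its direction depends on whether the session falls before or after the day 1 sample, and no timing is given.
- That the comparisons would reverse. Under the assumptions above, this needs more than 90% masking for fDGF (more than 80% if q = 20%), or dialysis adding more than 0.5 to CRR5.
- That 1.5–6.0 points is an estimate of the bias. It rests on p = 1 and a ratio near 1.

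The stakes are also limited. The primary outcome counts dialysis itself as failure, duration of DGF is a separate outcome, and for fDGF and CRR5 the distortion works against EVNP, so it would not create a false benefit. Finally, the remedy has a price. The article calls dialysis-defined DGF subjective and the trial is unblinded, so counting dialysis as failure brings that decision into creatinine-based outcomes. This stands, and is a reason to keep the creatinine-only analysis alongside.

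**Conclusion.** The concern holds for fDGF and CRR5. As defined, repeated dialysis can turn a DGF-positive patient fDGF-negative, and dialysis raises CRR5. If dialysis differs by arm as planned, both comparisons are pulled towards the null. CRR2 is distorted as well, but its direction cannot be stated.

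The size cannot be derived from the document. Only the 50% and 35% are its own figures; kinetics, session timing, masking share and true CRR means are all assumed. If the arms turn out to have similar dialysis use and timing, the problem is mainly loss of meaning in the measures and much less a bias between arms. The primary analysis and the sample size are unaffected. This should be changed, but it does not threaten the main result.

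**What to change.** Add a dialysis rule to the definitions, and fix it before outcome data are examined by arm:

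- **fDGF:** count any patient dialysed in the first 7 days as having fDGF.
- **CRR2 and CRR5:** give patients dialysed, or with graft loss or death, on or before day 2 (CRR2) or day 5 (CRR5) the worst rank, and compare arms with a rank-sum test in place of the t-test.
- **Sensitivity analysis:** keep the creatinine-only versions as now written, and report both.

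The cost is mainly wording, because dialysis in the first week must be recorded for the primary outcome; its date is needed to apply the day 2 and day 5 cut-offs. There are three downsides. CRR results are on ranks instead of mean differences. fDGF then contains the primary endpoint, so it is less independent of it. And the unblinded decision to dialyse enters outcomes that were based on creatinine alone. The sensitivity analysis shows how far the last two matter.

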### Randomisation

Patients will be allocated at random in a 1:1 ratio to either static cold storage (CS) plus 1 hour of EVNP (n=200) or CS (n=200) only. A patient information sheet will be given to potential recruits on admission for DCD kidney transplantation and written informed consent will then be obtained (see online supplementary appendices 1 and 2). Randomisation will be performed after the transplant recipient and kidney have both arrived in the transplanting centre and a final decision to proceed with transplantation has been made by a member of the study team. The randomisation will be performed on a web-based system (sealed envelope) which uses a computer-generated randomisation sequence. In cases where paired kidneys from the same donor are transplanted in the same centre, one kidney from the pair will be randomly allocated to CS and the other to EVNP. In these cases, the randomisation will also determine which kidney (right or left) will be transplanted first. Owing to the nature of the trial, no one is blinded to treatment allocation.

10.1136/bmjopen-2016-012237.supp1supplementary appendix

10.1136/bmjopen-2016-012237.supp2supplementary appendix

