#### Analysis population and principles

The population used for efficacy analyses will be an intent-to-treat population including all eligible randomised patients. This will be the primary analysis for the trial. Characteristics of all randomised patients will be tabulated by arm of the trial to describe the cohort.

The primary and secondary outcomes will also be analysed per protocol.

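### The protocol both forbids and permits use of the EVNP score in deciding whether a kidney is transplanted; the permitting sentence should go

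*Protocol article*

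**What the plan says.** Three places in the protocol article bear on whether the score may influence implantation.

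- **EVNP assessment scoring:** the score is recorded for every perfused kidney but "will not be used to make decisions about the suitability of kidneys for transplantation". It is built from findings during perfusion: "Scores for macroscopic appearance, renal blood flow and urine output will be added to yield an overall assessment score".
- **Secondary outcome measures:** "A clinical decision on the suitability of the kidney for transplantation will be made using normal criteria prior to perfusion". The next sentence reads: "However, the EVNP assessment score will be taken into consideration".
- **Randomisation:** allocation takes place only once recipient and kidney are at the centre and "a final decision to proceed with transplantation has been made by a member of the study team". The same section states that "no one is blinded to treatment allocation".

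The efficacy analysis uses "an intent-to-treat population including all eligible randomised patients" (Analysis population and principles). The primary outcome is dialysis within 7 days after transplantation. No score cut-off, decline step or replacement procedure appears anywhere in the article.

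**The concern.** Two operative sentences give opposite instructions on the same decision, and four centres have to follow them. The score exists only after randomisation and only in the EVNP arm, and the staff who see it know the allocation. If a centre took the later sentence as permission and declined a badly perfusing kidney, the EVNP arm would pass through a quality filter that the cold-storage arm cannot have.

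Intention to treat does not fully repair this. The recipient stays in the analysis set, but without a transplant there is no 7-day post-transplant DGF status to analyse. If declined kidneys carry a higher than average DGF risk and their recipients drop out of the comparison, the result is biased in favour of EVNP. The planned evaluation of how well the score predicts graft function would also lose the worst-scoring kidneys, which are the ones it most needs.

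**Working it through.** **Comparing the texts**

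1. EVNP assessment scoring: the score is recorded and plays no part in suitability.
2. Secondary outcome measures, first sentence on suitability: the decision is made on ordinary criteria, before perfusion.
3. Secondary outcome measures, next sentence: it opens with a contrast to the sentence before it and says the score will be considered. That preceding sentence concerns suitability, so the natural reading is that the score may modify the decision.
4. Randomisation: the final decision to proceed comes before allocation, hence before any perfusion and before any score.

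Statements 1, 2 and 4 agree. Statement 3 conflicts with each of them. Removing it makes the text consistent. Changing statement 1 to permit use of the score would leave a conflict with statements 2 and 4.

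**Illustration of what is at stake**

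Inputs from Sample size determination: control DGF rate 50%; design difference 50% − 35% = 15 points; α = 0.05 (sidedness not stated, two-sided assumed); 376 evaluable patients, which gives 376/(1 − 0.06) = 400 recruited, as stated. At 1:1 allocation that is 376/2 = 188 evaluable per arm.

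Assumptions not in the document: no true effect; a fraction *k* of EVNP kidneys declined; DGF risk *r* in those kidneys had they been implanted; their recipients left out for want of an outcome; an unadjusted pooled two-proportion z-test. The planned analysis is logistic regression adjusted for cold ischaemic time and donor age, so this is an approximation.

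Observed EVNP rate: p = (0.50 − k·r)/(1 − k). Spurious reduction: d = 0.50 − p. EVNP number analysed: 188(1 − k), which is about 184, 179 and 169 for k = 2%, 5% and 10%.

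Rejection probability: Φ[(d − 1.96·s0)/s1] + Φ[(−d − 1.96·s0)/s1], with s0 the pooled and s1 the unpooled standard error of the difference.

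Example, k = 0.10 and r = 1.0:
- p = (0.50 − 0.10)/0.90 = 0.4444, so d = 0.0556.
- Pooled rate = (188 × 0.50 + 169.2 × 0.4444)/357.2 = 0.4737, so s0 = 0.0529 and s1 = 0.0528.
- Rejection probability = Φ(−0.91) + Φ(−3.02) = 0.182.

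| Declined, k | r = 0.5 | r = 0.8 | r = 1.0 |
|---|---|---|---|
| 2% | 0 points; 5.0% | 0.61 points; 5.2% | 1.02 points; 5.4% |
| 5% | 0 points; 5.0% | 1.58 points; 6.0% | 2.63 points; 7.9% |
| 10% | 0 points; 5.0% | 3.33 points; 9.6% | 5.56 points; 18.2% |

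Each cell gives the spurious DGF reduction and the two-sided type I error. With 200 per arm instead of 188, the largest value becomes 19.1%.

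**The case against.** The strongest reply is that the protocol already rules out score-based declines three times over, and that no threshold or discard procedure exists. The harm then needs a centre to act on one stray sentence against the rest of the text. This stands as a limit on the finding: the defect is a contradictory rule and not a planned discard step.

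The sentence might also be only a loose pointer to the analysis of the score's predictive value. That is possible but less natural, because that evaluation has already been stated two sentences earlier and the contrast attaches to the suitability decision. A site could reasonably read it as permission either way.

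The section Analysis population and missing data promises sensitivity analyses for patients with unknown DGF status. It covers withdrawal and death, does not name kidneys that are not implanted, and a sensitivity analysis would not remove the bias from the primary result.

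The numbers rest on assumed decline rates and risks, and 18.2% is the extreme corner. That is correct, and the finding does not depend on them.

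Finally, the sponsor may have wanted to leave surgeons discretion over a kidney that perfuses very badly. The document does not show this, and discretion based on the score is what the scoring section already excludes.

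**Conclusion.** The concern holds. The protocol states opposite rules on whether the EVNP score may affect the decision to transplant, and the sentence under Secondary outcome measures is the one that is wrong as written. It should be fixed, because it bears on which randomised kidneys are implanted and so on the primary comparison.

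The size of any bias cannot be established from the document: it gives neither a decline rate nor a DGF risk for declined kidneys. The bias is zero if the scoring section is followed, and also if declined kidneys have only average risk. Under the stated assumptions it is negligible at 2% declined, modest at 5%, and material only near 10% with a high risk in the declined kidneys. Even there, the spurious difference of 5.6 points is a little over a third of the 15-point design difference (5.56/15 = 0.37).

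**What to change.** Delete the sentence "However, the EVNP assessment score will be taken into consideration" from Secondary outcome measures. The rule under EVNP assessment scoring then governs: the score is recorded and not used for suitability, in line with a final decision taken before randomisation.

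If a kidney is nonetheless not implanted after randomisation, keep the recipient in the intention-to-treat set and report the case by arm with the reason. The outcome rule for such a recipient and any sensitivity analysis can be left to the SAP.

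The cost is one deleted sentence, with no extra patients, procedures or analyses and no change to the sample size. The only thing given up is a discretion that the scoring section already rules out.
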